### Assignment and Blinding

A PT aide who schedules patient appointments assigns each prescreened patient to one of the four PTs who deliver the interventions, depending their open schedule. If a patient is eligible, then he/she undergoes the intervention with the assigned PT. Thus, although the patients are not randomly assigned to each group, this approach was practical for the clinic and avoided selective enrollment assignment since the PT aide assigns an upcoming patient to a PT according to schedule availability without regard to diagnosis, age, or sex. To prevent performance bias, the four treating PTs were distributed into two groups: two PTs provide traditional physical therapy for 100 participants, while the two other PTs provide feedback-based therapy for the other 100 participants. We do not anticipate any selection bias and we do expect equal number of subjects to be assigned to each of the four PTs. Furthermore, information that could introduce bias are withheld from subjects in both groups, i.e., their informed consent does not mention efficacy of feedback-based therapy. To prevent bias due to varying levels of PTs experience, one very experienced PT (>10 years working with patients) and one less experienced PT (<5 years working experience) were assigned to use Mobility Rehab and a similar stratification of experienced and inexperienced PTs were assigned to not use Mobility Rehab. Detection bias is avoided by blinding the PT assistants who administer the pre- and post-assessments and by blinding the investigators and statisticians at OHSU who are analyzing the results regarding subjects' group assignment.

Although we are not assessing blinding by the outcome assessors, the following measures are implemented to avoid assessors from gaining impressions/information about treatment assignment: assessors are based in a different building from the one where the interventions are carried out and, therefore, they do not see patients during rehabilitation sessions and; participants are asked to refrain from mentioning their group allocation to assessors.

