## Abstract

**Introduction:** Mobility impairments are among the main causes of falls in older adults and patients with neurological diseases, leading to functional dependence and substantial health care costs. Feedback-based interventions applied in controlled, laboratory environments have shown promising results for mobility rehabilitation, enhancing the benefits of standard therapy. However, the effectiveness of sensor-based feedback to improve gait in actual outpatient physical therapy settings is unknown. The proposed trial examines the effectiveness of a physical therapist-assisted, visual feedback system using wearable inertial sensors, Mobility Rehab, for mobility training in older adults with gait disturbances in an outpatient clinic.

**Methods:** The study is a single site, pragmatic clinical trial in older adults with gait disturbances. Two hundred patients undergoing their outpatient rehabilitation program are assigned, by an independent assistant, for screening by one of four therapists, and assigned to either a standard physical therapy or therapist-assisted feedback therapy. Both groups train twice a week for 6 weeks. Four physical therapists were randomized and stratified by years of experience to deliver standard therapy or therapist-assisted feedback rehabilitation. Each session is 45 min long. Gait is trained for 30 min. The additional 15 min include exercises for endurance, strength, and static and dynamic balance in functional tasks. Mobility Rehab uses unobtrusive, inertial sensors on the feet and belt with real-time algorithms to provide real-time feedback on gait metrics (i.e., gait speed, double support time, foot clearance, angle at foot strike, and arm swing), which are displayed on a hand-held monitor. Blinded assessments are carried out before and after the intervention. The primary outcome measure is subjects' perception of balance as measured by the Activities-specific Balance Confidence scale. Gait speed, as measured with wearable inertial sensors during walking, is the secondary outcome measure.

**Discussion:** We hypothesize that therapist-assisted feedback rehabilitation will be more effective than standard rehabilitation for gait. Feedback of motor performance plays a crucial role in rehabilitation and objective characterization of gait impairments by Mobility Rehab has the potential to improve the accuracy of patient-specific gait feedback.

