## Methods and Analysis

### Trial Design

The study is a single-site, pragmatic, controlled clinical trial in older people with gait disturbances. The trial compares standard-of-care gait training by PTs with therapist-assisted feedback therapy using Mobility Rehab in the same clinic. Participants scheduled at the physical therapy clinic for gait training are assigned to one of the four PTs, and that will determine, if eligible, their group assignment for the duration of their outpatient therapy. Assessments occur at baseline (pre) before intervention starts and immediately after the last session of intervention (post). The trial design is illustrated in Figure 1. This protocol paper follows the SPIRIT (Standard Protocol Items: Recommendations for Interventional Trials) 2013 statement and guidelines (22). SPIRIT template for the schedule of enrollment, interventions, and assessments is presented in Figure 2.

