### Recruitment and Screening

Outpatients coming for gait training at the Northwest Rehabilitation Associates clinic are invited to participate in this trial. Those who agree to learn more about the study are seen by a PT aide who explains the study further, completes a screening interview (for exclusion and inclusion), supervised by an experienced PT (MS), and obtains consent. There are no gender, ethnic, or racial minority exclusions for this study. Inclusion criteria include: 60–89 years old and gait disturbances requiring physical therapy. Any disease may be included and efforts are made to maintain an equal number of women and men in the sample. Participants are included in the study if they are able to follow instructions (up to the PT's judgement). This trial will stop enrolling participants when 200 individuals will have completed baseline and follow-up assessment.

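### Booking by open schedule does not fix the arm when PTs of both arms are free, so the no-selection-bias statement lacks support; a random draw among the open PTs would be a cheap improvement

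*Protocol article*

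**What the plan says.** Under Assignment and Blinding, the aide who schedules appointments "assigns each prescreened patient to one of the four PTs who deliver the interventions, depending their open schedule". Trial Design says that patients are "assigned to one of the four PTs, and that will determine, if eligible, their group assignment for the duration of their outpatient therapy". Each PT's arm is fixed, with two PTs per arm, so booking a PT also sets the arm.

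The article is open about this: "although the patients are not randomly assigned to each group, this approach was practical for the clinic". Its safeguard is that the aide "assigns an upcoming patient to a PT according to schedule availability without regard to diagnosis, age, or sex". The Abstract adds that patients "are assigned, by an independent assistant, for screening by one of four therapists". From this the article concludes: "We do not anticipate any selection bias and we do expect equal number of subjects to be assigned to each of the four PTs".

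Eligibility is applied after the PT has been assigned. Under Recruitment and Screening, one criterion is that participants are "able to follow instructions (up to the PT's judgement"; which PT judges is not stated. Statistical Analysis adjusts post-assessment ABC for age, gender and pathology. Neither baseline ABC nor gait severity is listed.

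**The concern.** Only four PTs were randomised, so therapist randomisation cannot be relied on to balance the patients' case mix. At patient level the comparison depends on how bookings are made. Availability is a good rule when it leaves no choice. When it does leave one, the article states an intention and no mechanism. The intention names three traits and omits gait severity, fall history and a request for a particular PT.

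If bookings followed any of these, the arms would differ before treatment and the difference would pass into the primary comparison. The plan's only reason for not randomising patients is practicality in the clinic. That reason does not apply to bookings where several PTs are free anyway.

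**Working it through.** **1. When does the stated rule fix the arm?** There are four PTs, two per arm.

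- One PT open: PT and arm are both fixed.
- Two PTs open: of the 6 possible pairs, 2 lie within an arm (arm fixed) and 2 × 2 = 4 cross the arms (arm not fixed).
- Three or four PTs open: both arms are always represented, so the arm is not fixed.

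The article does not say how often each case occurs.

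**2. What protects those bookings?** The assurance covers diagnosis, age and sex. The model covers age, gender and pathology. These are essentially the same three traits, so a characteristic outside them is covered by neither, except as far as it correlates with them.

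**3. The plan's own power figure, and whether a random draw would alter it.** From Sample Size and Power Analysis: m = 50, four therapists, ICC = 0.002, type 1 error 0.05 (two-sided assumed).

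- DEFF = 1 + 49 × 0.002 = 1.098, and ESS = 200 / 1.098 = 182.1.
- Noncentrality = effect size × √182.1 / 2, which is 6.07 at 0.9 SD and 8.10 at 1.2 SD.
- A noncentral t with 4 − 2 = 2 degrees of freedom gives power of 84.3% and 96.1%, as stated in the article.

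A draw restricted to open PTs changes none of these inputs, provided that about 50 patients per PT is kept.

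**4. Possible size (illustration; the steering inputs are assumed).** Let s be the share of patients with PTs of both arms open. Among them, the better-prognosis half goes to one arm with probability 0.5 + q. Let g be the ABC gap between the halves. With equal arms, the better half makes up 0.5 + sq of one arm and 0.5 − sq of the other, so the spurious difference is 2 × s × q × g.

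| s | q | g = 10 | g = 16 | g = 24 |
|---|---|---|---|---|
| 0.25 | 0.05 | 0.25 | 0.4 | 0.6 |
| 0.50 | 0.10 | 1.0 | 1.6 | 2.4 |
| 0.75 | 0.20 | 3.0 | 4.8 | 7.2 |

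For scale, a perfect split of a normal baseline ABC at its median gives g = 2 × SD × √(2/π), which is 17.6, 23.9 and 31.9 for SD 11, 15 and 20. The plan's SD range is 11 to 20; 15 is an intermediate value. With a random draw q = 0, and this component is zero in expectation.

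**5. How much steering would larger figures need?** Take the plan's baseline mean of 60 with SD 11 / 15 / 20, and assume normality. The share p below 50 is 18.2 / 25.2 / 30.9%, and these patients average 19.5 / 25.4 / 33.0 points less than the rest. If a share 0.5 + q of the below-50 patients with both arms open go to one arm, the proportion below 50 differs between arms by 4 × p × s × q. Take s = 0.5 (assumed).

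- A 10-percentage-point shift gives 2.0 / 2.5 / 3.3 ABC points. It needs about 77 / 70 / 66% of those patients sent to one arm.
- A 20-point shift is impossible at SD 11, where total steering (q = 0.5) yields 4 × 0.182 × 0.5 × 0.5 = 18.2 points. At SD 15 / 20 it needs about 90 / 82%.

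Steps 4 and 5 carry the baseline gap in full to post-assessment and credit nothing to the covariate adjustment, so they lean high.

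**The case against.** The strongest reply is that nothing in the article shows a discretionary choice. Following schedule availability is compatible with a fixed rule such as the earliest open slot. The article condenses a fuller protocol, where a booking rule may sit. The assigner is described as independent, and nothing says that the aide sees severity or ABC scores, which blinded assistants collect in another building. The design is disclosed, reasoned and modelled as therapist-level randomisation.

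Much of this stands. A reader might infer that the aide hand-picks among free PTs, or that sending harder patients to certain PTs is normal clinic practice. The article supports neither. A reader might also expect difficult patients to go to the experienced PT. Each arm has one PT with more than 10 years and one with less than 5, so such steering would mostly move patients between PTs within an arm, although a choice between the two experienced PTs is still a choice of arm.

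What does not stand is the step from this to no selection bias. The procedure is described in the article and the conclusion is drawn there, so the point is not a missing detail. A fixed tie rule held elsewhere would narrow the gap. A random one would sit badly with the statement that patients are not randomly assigned. Practicality does not answer the point either, since a draw among PTs who are already open uses the same slots.

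**Conclusion.** The point holds as a cheap improvement to the design and a correction to an over-firm statement. Whenever PTs of both arms are open, the stated rule does not determine the arm. The assurance and the adjustment cover essentially the same three traits, and selection on severity or baseline ABC would go uncorrected.

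The size is unknown. Under the assumed inputs it runs from 0.25 to 7.2 ABC points, with 1.6 at the middle values (s = 0.5, q = 0.10, g = 16). One might go further and say that the bias could reach a third to a half of the 12-point target. That takes a 20-point shift in the share below 50, which no figure in the article supports and which needs extreme steering. Nor does the article show that any steering has occurred.

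**What to change.** Amend Assignment and Blinding along these lines:

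- For each new patient, record which PTs have a slot that fits, before any allocation is revealed. This order matters, because discretion could otherwise move to who is listed as open.
- If more than one PT is open, take the PT from a concealed, pre-generated random list restricted to those PTs and balanced towards about 50 patients per PT. Log the PT drawn.
- If only one PT is open, book as now and flag the patient.
- Add a sensitivity analysis in the patients allocated by chance.
- Replace the no-selection-bias statement with a qualified one. Patients with a single open PT, and eligibility judged after the PT is assigned, remain unprotected.

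The cost is preparing the list, one log line per booking and some loss of scheduling freedom. Sample size, number of therapists and power calculation are unchanged. The article does not show whether enrolment is still open. If the change comes mid-trial, there will be two allocation periods, to be identified in the analysis. The change does not resolve the confounding of therapist and arm that comes with two PTs per arm.

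### Patients are tied to a therapist, and so to an arm, before eligibility is confirmed, with no concealment described; the assurance of no selection bias is therefore unsupported

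*Protocol article*

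**What the plan says.** Four parts of the Protocol article bear on the order of steps and on who decides.

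- **Abstract, Methods:** patients "are assigned, by an independent assistant, for screening by one of four therapists".
- **Trial Design:** each patient booked at the clinic to train gait is "assigned to one of the four PTs, and that will determine, if eligible, their group assignment for the duration of their outpatient therapy".
- **Recruitment and Screening:** a PT aide conducts the screening interview and takes consent, supervised by an experienced PT. "Participants are included in the study if they are able to follow instructions", which is left to the judgement of a PT who is not further identified.
- **Assignment and Blinding:** the scheduling aide "assigns each prescreened patient to one of the four PTs who deliver the interventions, depending their open schedule". Then: "If a patient is eligible, then he/she undergoes the intervention with the assigned PT". The section says openly that patients are not randomised. It argues that allocation by open slot, ignoring diagnosis, age and sex, avoids selective enrolment, and concludes: "We do not anticipate any selection bias".

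Under Statistical Analysis, the post-treatment ABC comparison is adjusted for age, gender and pathology, with a random effect for PT. Baseline ABC is not among the listed covariates.

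**The concern.** Two PTs deliver each arm, so naming the PT names the arm. If the arm is known while someone is still deciding whether the patient qualifies or is being asked to consent, that knowledge can influence who enters. This is post-allocation identification (recruitment) bias. Neither a fair choice of PT nor a random effect for PT removes it, because it acts on the make-up of the arms.

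The opening is widest where a criterion is subjective. Ability to follow instructions is such a criterion, and it is plausibly related to how a patient scores and responds. If it is applied differently in the two arms, part of the difference in post-treatment ABC reflects who was admitted rather than what was delivered. The article gives a firm assurance on this point, and its stated reason does not reach the step at risk.

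**Working it through.** **1. Order of steps.** Three sections are set side by side.

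| Section | Comes first | Comes afterwards |
|---|---|---|
| Abstract | assignment by an assistant | screening by one of four therapists |
| Trial Design | assignment to a PT, which sets the group | eligibility (the group holds if eligible) |
| Assignment and Blinding | PT slot given to a prescreened patient | eligibility, then treatment with that PT |

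All three put final eligibility after the PT is known. The third shows that some screening comes earlier, but not how much.

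**2. Who decides.** The Abstract points to the treating therapists: "for screening by one of four therapists". Recruitment and Screening points to an aide under one experienced PT. That section does not say whether the PT who judges ability to follow instructions is the supervisor or the assigned therapist. The two accounts cannot both be complete.

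**3. What the safeguards cover.**
- Scheduling without regard to diagnosis, age or sex covers which PT a patient gets. It does not cover enrolment after that.
- Leaving efficacy out of the consent form covers patient expectation, not staff discretion.
- Blinding of assessors and analysts covers measurement and analysis, not entry.
- No section describes concealing the assigned PT from those who judge eligibility or obtain consent.

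**4. Size, as an illustration only.** The article states no figure for selection, so there is none to reproduce. From Sample Size and Power Analysis: ABC SD 11–20, target difference 12 points. My assumptions: a fraction q = 0.05 or 0.10 is excluded in one arm only and none in the other; exclusion takes the lowest part of a normally distributed trait; the trait correlates ρ = 0.2 to 0.5 with ABC.

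Shift in the arm mean, in SD units = ρ × φ(z_q) / (1 − q), where φ(z_q)/(1 − q) is 0.109 at q = 0.05 and 0.195 at q = 0.10.

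| q | ρ | Shift (SD) | Points, SD 11 | Points, SD 20 |
|---|---|---|---|---|
| 0.05 | 0.2 | 0.022 | 0.24 | 0.43 |
| 0.05 | 0.5 | 0.054 | 0.60 | 1.09 |
| 0.10 | 0.2 | 0.039 | 0.43 | 0.78 |
| 0.10 | 0.5 | 0.097 | 1.07 | 1.95 |

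The largest entry is 1.95/12 = 0.16 of the target, about one sixth. The sign reverses if the exclusions fall in the other arm or at the other end of the trait.

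**5. Effect on the error rate.** Using the article's own formulae at ICC 0.002, DEFF = 1 + 49 × 0.002 = 1.098 and effective sample size = 200/1.098 = 182.1. A two-sided 5% noncentral t test with 2 df (four therapists minus two arms) reproduces the stated power: 84.3% at 0.9 SD and 96.1% at 1.2 SD. The same test with no true effect, but with the shifts in the table, has a rejection rate of about 5.1% to 7.0% instead of 5%.

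**The case against.** The best defence has four parts.

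- **The judging PT may be the supervisor.** The only PT whom Recruitment and Screening has introduced by that point is the experienced supervisor. If that person applies the criterion to everyone, the risk of different standards by arm falls sharply. This reading is natural and may be right. It conflicts with the Abstract, though, and it does not change the order of steps or conceal the arm from the supervisor or the aide.
- **Patients are prescreened.** Most exclusions may therefore precede assignment. That is possible, but the extent is not stated. The flowchart and schedule figures, not available to this review, may show more.
- **The design is openly pragmatic.** Allocation by schedule is disclosed as a practical choice and is not faulted here. The point concerns what happens after the slot is given.
- **The effect is small.** Under the assumptions above, that is correct.

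A reader might infer more than the text allows:

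- **That the bias favours feedback**, because therapists using a tablet would want more capable patients. The documents do not support a direction. The Introduction presents the tablet as a tool that helps the therapist give verbal instructions, and the demanding gait tasks under Interventions are not confined to one arm.
- **That the shift could reach a third of the target**: 0.195 × 20 = 3.9 points, against 12. That needs 10% excluded on ABC itself (correlation 1), but the criterion is ability to follow instructions.
- **That the effort to balance women and men operates after the arm is known.** The article does not say when it is applied, and gender is in the model.

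**Conclusion.** The point holds in a limited form. The article describes an unprotected route to differential enrolment; it does not show that bias has occurred or which way it would run. The conclusion that no selection bias is expected does not follow from the reason given, and the accounts of who screens, and when, conflict.

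Under the illustrative assumptions (5–10% excluded in one arm only, correlation 0.2–0.5, normal trait), the distortion is about 0.02–0.10 SD: 0.2–1.1 ABC points at SD 11 and 0.4–2.0 at SD 20. That is small against 12 points but not zero. The listed covariates would remove at most the part explained by age, gender and pathology. The order of steps is firm on the text; how far the arm influences the judgement in practice depends on who makes it, which the article leaves unresolved.

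**What to change.** 1. Reconcile the Abstract, Recruitment and Screening, and Assignment and Blinding on who screens, which PT makes the instruction-following judgement, and what is complete when a patient counts as prescreened.
2. Have the aide and the supervising PT complete every eligibility judgement and obtain consent before a PT slot is looked up. Treating PTs should have no role in inclusion.
3. Add baseline ABC to the primary model. Trial Design already has an assessment before treatment, so no new data are needed. It corrects imbalance in baseline ABC itself, though not in unmeasured traits that affect response.
4. For patients already assigned under the current order, report the numbers screened and not enrolled by assigned PT.
5. Replace the no-selection-bias statement with an acknowledgement of the risk and of the steps taken against it.

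The cost is a minor change in the order of clinic paperwork, using existing staff, and one more covariate. Allocation by open schedule can stay. The new order cannot reach patients already enrolled; for them, steps 3 and 4 are what remains.

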### Interventions

The two rehabilitation interventions for gait disturbances are: (1) standard-of-care physical therapy and (2) therapist-assisted feedback physical therapy. Both groups train twice a week for 6 weeks. Sessions are 45 min long and gait (with or without Mobility Rehab) is trained for 30 min in each session. The additional 15 min include exercises for endurance, strength, and static and dynamic balance in functional tasks. The difference between the two groups is the use of the Mobility Rehab system in the therapist-assisted feedback group. PTs design their own treatment plan for each patient. They are allowed to select modality, overground walking and/or treadmill, and tasks (dual task, head turns, etc.) as appropriate for each patient. During a regular session, patients work on gait with the following tasks for 30 min: weights on ankles, dual tasks, upper extremity support, partial body weight support, speed challenges, direction changes, obstacles, and head turning. The PTs using Mobility Rehab system underwent specific training on how to effectively use the system (e.g., sensors placement, software navigation, selection and interpretation of metrics, etc.) before the start of the trial.

The Mobility Rehab system uses unobtrusive, wearable, inertial sensors with real-time algorithms to provide real-time feedback on five gait metrics: step duration, stride length, arm range of motion, trunk coronal range of motion, and elevation at midswing (Figure 3). Therapists are allowed to select any gait metric and to focus on one or several gait metrics. The visual feedback is provided to a hand-held monitor/tablet (Figure 3) and displayed relative to age-specific normative values, which were previously collected from 120 healthy subjects between the ages of 60 and 89 years during a 2-min overground walk at a comfortable pace. Therapists also can select a minimum and maximum goal for a metric, based on each patient's abilities.

